## Abstract

**Background:**

Due to the strong reduction in the length of hospital stays in the last decade, the period of in-hospital postoperative care is limited. After discharge from the hospital, guidance and monitoring on recovery and resumption of (work) activities are usually not provided. As a consequence, return to normal activities and work after surgery is hampered, leading to a lower quality of life and higher costs due to productivity loss and increased health care consumption.

**Objective:**

With this study we aim to evaluate whether an eHealth care program can improve perioperative health care in patients undergoing commonly applied abdominal surgical procedures, leading to accelerated recovery and to a reduction in costs in comparison to usual care.

**Methods:**

This is a multicenter randomized, single-blinded, controlled trial. At least 308 patients between 18 and 75 years old who are on the waiting list for a laparoscopic cholecystectomy, inguinal hernia surgery, or laparoscopic adnexal surgery for a benign indication will be included. Patients will be randomized to an intervention or control group. The intervention group will have access to an innovative, perioperative eHealth care program. This intervention program consists of a website, mobile phone app, and activity tracker. It aims to improve patient self-management and empowerment by providing guidance to patients in the weeks before and after surgery. The control group will receive usual care and will have access to a nonintervention (standard) website consisting of the digital information brochure about the surgical procedure being performed. Patients are asked to complete questionnaires at 5 moments during the first 6 months after surgery. The primary outcome measure is time to return to normal activities based on a patient-specific set of 8 activities selected from the Patient-Reported Outcomes Measurement Information System (PROMIS) physical functioning item bank version 1.2. Secondary outcomes include social participation, self-rated health, duration of return to work, physical activity, length of recovery, pain intensity, and patient satisfaction. In addition, an economic evaluation alongside this randomized controlled trial will be performed from the societal and health care perspective. All statistical analyses will be conducted according to the intention-to-treat principle.

**Results:**

The enrollment of patients started in September 2015. The follow-up period will be completed in February 2017. Data cleaning and analyses have not begun as of the time this article was submitted.

**Conclusions:**

We hypothesize that patients receiving the intervention program will resume their normal activities sooner than patients in the control group and costs will be lower.

**ClinicalTrial:**

Netherlands Trial Registry NTC4699; http://www.trialregister.nl/trialreg/admin/rctview.asp?TC=4699 (Archived by WebCite at http://www.webcitation.org/6mcCBZmwy)

## Introduction

Between 1993 and 2013 the number of surgical procedures per year at community hospitals in the United States increased by 16.5% to more than 26 million per year [1]. This is partly due to the growing trend in day care surgery (ambulatory surgery). This is illustrated by the fact that in 2013 the number of surgeries performed in day care (17.4 million, 65.6%) exceeded the number of surgeries performed in overnight stay (9.1 million, 34.4%) [1]. Due to the strong reduction in the length of hospital stay, perioperative in-hospital care has been reduced accordingly. Once patients have been discharged, the degree of guidance and monitoring on recovery is limited, and sometimes conflicting advice is given by the different health care providers involved in the recovery process [2-5]. In addition, patients do not always know who to contact for support in case of postoperative complaints. This poor guidance and transition of perioperative care after hospital discharge contributes to patient uncertainties and postoperative fear that may hamper their recovery [6,7]. As a consequence, return to normal activities, including work, after surgery takes much longer than expected [8,9]. The delayed recovery has a negative impact on quality of life, clinical outcomes, and medical consumption and increases the risk of work disability, leading to an increased risk of mental health problems and poor general health [10,11]. In terms of the burden on society, this increases costs: costs resulting from the increased medical consumption (direct costs) and costs in relation to the high productivity loss due to prolonged sick leave (indirect costs) [10].

Therefore, improving the quality of perioperative care may contribute to accelerated recovery and health care efficiency, which in turn may reduce health care costs. eHealth seems to be an effective tool in this process for several reasons. First, electronic devices are widely available and are increasingly popular. This means that patients can be easily reached using this medium. Second, there is an increasing demand for self-management in society; eHealth has the potential to motivate people and turn them into more active and effective managers of their own health [12,13]. Finally, eHealth is a useful tool to provide the patients with tailored information, by providing only advice based on the patient’s profile. Therefore an eHealth care program has been developed to improve perioperative care after gynecological surgery [14]. The program was developed using an intervention mapping protocol, based on a systemic review of the literature, input of patients during focus groups, and consented guidelines on resumption of activities after surgery achieved after a Delphi procedure [14,15]. The effect of the eHealth care program on return to work was evaluated in a randomized controlled trial (RCT). Patients who had access to the care program returned to work 9 days earlier than patients from the control group [16]. Because of these promising results, the care program was further developed for a broader population, according to the wishes and preferences of a sample of patients who had undergone various types of abdominal surgery. While the gynecological care program aimed to deliver additional care by providing extra support and information through eHealth, this adapted care program also aims to partly substitute perioperative care with eHealth. In addition, the care program will focus on health-behavior change techniques using an activity tracker, which has been described before as an effective strategy [17,18]. With this multicenter, single-blinded, RCT, we will evaluate whether this adapted perioperative eHealth program will be effective and cost effective as compared to usual care on the resumption of normal activities in patients undergoing commonly applied minor abdominal surgical procedures with a short duration of hospital stay.

## Methods

### Study Setting

Patients will be included from the surgical and gynecological departments of 7 teaching hospitals in the Netherlands. The trial was conducted in accordance with the Standard Protocol Items: Recommendations for Interventional Trials and reported in accordance with the Consolidated Standards of Reporting Trials [19-21]. The study was approved by the local medical ethics committee under registration number 2014.301 and by the institutional review boards of all participating hospitals. The study is registered at the Netherlands Trial Registry (NTR4699).

### Eligibility Criteria

Eligible patients for this study are adults from 18 to 75 years old who are on the waiting list for one of the following commonly applied minor surgical procedures: laparoscopic cholecystectomy, open or laparoscopic inguinal hernia surgery, or laparoscopic adnexal surgery. Participants meeting any of the exclusion criteria will not be considered (Textbox 1).

Exclusion criteria.Exclusion criteria:Surgery without a curative intention or with additional radio- or chemotherapyDeep infiltrating endometriosisEctopic pregnancyAdnexal surgery because of pelvic inflammatory disease or tubal ovarian abscessCombination of several surgical proceduresSevere comorbidity which might complicate the postoperative coursePatient who are unable to understand the information from the studyInsufficient understanding or ability to complete questionnaires in Dutch

### Interventions

#### Control Group

Patients allocated to the control group will receive usual care and access to the nonintervention part of the website (www.ikherstel.nl). On this part of the website, the patient information brochure about the surgical procedure from the hospital where the patient will have surgery is presented. This is the same brochure as the one patients often receive in various hospitals when they are scheduled for surgery. The only reason to give patients access to this website is to minimize the bias in estimation of the intervention effect. Furthermore, pre- and postoperative care will be given according to the local protocol of the hospital. In the Netherlands, patients do not receive structural and detailed instructions about the resumption of normal activities including work. Usually, after the patient is discharged from the hospital, an outpatient postoperative consultation is scheduled 4 to 8 weeks following surgery.

#### Intervention Group

Patients in the intervention group will receive access to the intervention part of the website, a mobile application, and an activity tracker. Table 1 provides an overview of the different components of the intervention.

**Table 1 table1:** Components of the intervention.

Component	Target population	Content	Aim
Website	All patients of the intervention group	Information by text and animations^a^	Enhancing patient involvement and recovery expectations and reducing anxiety
		Making a personalized convalescence plan^a^	Creating recovery expectations and improving recovery
		Recovery monitor and recovery report^a^	Reducing uncertainties and fear related to the recovery process and improving monitoring of postoperative care
		eConsult	Increasing access to care, reducing patient uncertainties and fear related to the recovery process, and reducing costs and workload (by replacing the appointment in the outpatient clinic)
App	All patients of the intervention group with a smartphone	Information by text^a^	Enhancing patient involvement and recovery expectations and reducing anxiety
		Insight in the convalescence plan^a^	Creating recovery expectations and improving recovery
		Recovery monitor and recovery report^a^	Reducing uncertainties and fear related to the recovery process and improving monitoring and transition of postoperative care
		Creating a packing list	Helpful tool
		Section to make notes	Helpful tool
Activity tracker	All patients of the intervention group with a smartphone which can be linked to an activity tracker	Monitoring and giving feedback on recovery^a^	Reducing uncertainties and fear related to the recovery process, which may improve recovery

^a^Content is based on the intervention mapping study of Vonk Noordegraaf et al [14].

##### Website

The website aims to prepare patients in the best possible manner for their surgery and to offer guidance during their recovery process until full recovery and resumption of all daily activities are achieved. The following tools on the website will support this.

###### Providing Information About the Surgical Procedure and Recovery Process

On the website, information will be tailored to the patient, which offers the opportunity to enhance patient involvement (Figure 1) [13]. This is possible because some data are already prefilled when patients receive their website account (eg, surgical procedure, sex, hospital). The information will be offered by text as well as animations. The aim is to prepare the patient as well as possible for the day of surgery, which may contribute to the patient being more aware of what to expect and have a positive effect on anxiety and satisfaction [22]. In addition, it aims to improve recovery expectations, as expectations about the length of the recovery before surgery have proven to be an important predictor of the length of recovery [23]. After surgery, text and animations will be offered about the recovery period, which may support patients during this period and may help them with feelings of insecurity. Information about several postoperative complaints is available, including practical advice about when, how, and with whom patients should seek contact. We hypothesize that by providing this information, patients will be encouraged to resume their daily activities. In addition, this empowerment will help when deciding whether contact with a health care provider is indicated in case of complaints or complications during their recovery.

**Figure 1 figure1:**
[figure not shown]
Text and animations on the website (see Multimedia Appendix 1 for more information).

###### Making a Personalized Convalescence Plan

The most important tool on the website is the option to generate a personalized and tailored convalescence plan, including advice about resumption of daily (work) activities (Figures 2 and 3). Using a modified Delphi method, specific convalescence recommendations were developed for several types of abdominal surgical procedures [24,25]. The recommendations given are tailored to the patient and are based on the input of patients’ normal preoperative activities and the surgical technique (using algorithms). It aims to improve recovery, return to normal (work) activities, and quality of life. The convalescence plan will be approved electronically on the first postoperative day by the operating surgeon, resulting in a definitive convalescence plan. If complications occur during surgery, the surgeon will not approve the convalescence plan and the patient will receive a message that their initial convalescence plan is no longer applicable and that the adjusted instructions of the surgeon should be followed.

**Figure 2 figure2:**
[figure not shown]
Personalized convalescence plan (see Multimedia Appendix 1 for more information).

**Figure 3 figure3:**
[figure not shown]
Personalized convalescence plan displayed on a timeline (see Multimedia Appendix 1 for more information).

###### Getting Feedback on Recovery by a Recovery Monitor and Recovery Report

The recovery monitor and report are tools to identify recovery problems and give patients feedback on their recovery progress. Patients are asked to indicate by a recovery monitor to what extent they have resumed their activities (Figure 4), which is subsequently graphically displayed in a recovery report allowing them to track their progress (Figure 5). If patients report a delayed recovery, an alerting system advises them to contact a specific health care professional, depending on the underlying problem. It also aims to improve monitoring and transition of postoperative care; after the patient has given consent, the Web portal can be accessed by a health care provider in secondary care to monitor the patients’ recovery and thus identify recovery problems.

**Figure 4 figure4:**
[figure not shown]
Recovery monitor (see Multimedia Appendix 1 for more information).

**Figure 5 figure5:**
[figure not shown]
Recovery report (see Multimedia Appendix 1 for more information).

###### Postoperative Consult by eConsultation Instead of Consultation in the Outpatient Clinic

At discharge, patients from the intervention group will not receive a standard appointment at the outpatient clinic. Instead, they are offered continuous guidance via the website (information, feedback on recovery) and the possibility to ask questions on the website to a health care professional from their own hospital by means of an eConsult in case of recovery problems (Figure 6). They are informed that the question will be answered within 2 working days except for urgent matters. In that case, they receive a phone number for direct contact. In addition patients will receive a telephone call 2 weeks after surgery to inform them about any test results. Various studies already have proven that telephone follow-up is feasible and effective after the type of surgical procedures which are included in this study [26-28]. The telehealth follow-up aims to replace the standard single postoperative consultation in the outpatient clinic to increase access to care, reduce patient uncertainties and fear related to the recovery process, reduce costs and workload, and meet patient preferences of care during out-of-office hours [29,30]. We hypothesize that patients will be more comfortable and less hampered in resuming their activities with the opportunity to ask questions whenever they prefer instead of the standard consultation several weeks after surgery.

**Figure 6 figure6:**
[figure not shown]
eConsult (see Multimedia Appendix 1 for more information).

##### Mobile Phone App (mHealth) and Activity Tracker

All information which is available on the website is also available on the mobile phone app (Ikherstel app), which will be synchronized with the website. This mHealth app has been developed because of the increasing use of mobile phone apps and in order to make the intervention more accessible. This means that the convalescence plan that is created by the patient on the website will also be displayed on the app. In addition, the app will offer some extra features, such as a section to make notes and the option to compose a list of what to pack when being admitted to hospital (Figure 7). If patients do not have a smartphone they will only use the website. Patients who have a smartphone may also receive an activity tracker (UP MOVE, Jawbone). Not all kinds of smartphones can be linked to this activity tracker, so only a proportion of the patients will receive an activity tracker. This activity tracker measures daily step count. We performed a pilot study with an accelerometer in 30 patients who underwent surgery that showed that the step count had a clear correlation with activity intensity levels (data not yet published, personal communication). Patients can link the activity tracker to the app. The activity tracker will be used as an aid for patients to monitor and to give feedback on their recovery. Patients are instructed to wear the accelerometer from the seventh day before surgery until 3 weeks after surgery and during the sixth week after surgery. In the week before surgery a baseline measurement will be performed. The mean step count per day of this week will be set as their target postoperative activity level. In the app, it will be displayed on which date this target level is expected to be reached (Figure 8). This date is based on the convalesce plan which is developed by the patient. After surgery, the daily step count will be graphically displayed in the app and on the website as a percentage of their target activity level. When no baseline measurement is performed (for example, because the period between inclusion and surgery is shorter than 1 week), the target activity level will be set at 7100 steps per day (based on the mean preoperative value of the pilot study). As the pilot study also indicated that the most improvement in activity level was detected in the first 2 weeks after surgery, it was decided to ask the patients to wear the accelerometer during the first 3 weeks after surgery. The sixth week was chosen because we hypothesize that baseline activity level will be reached in this week. Patients will be offered the opportunity to wear the activity tracker in the fourth and fifth week after surgery as well.

**Figure 7 figure7:**
[figure not shown]
Mobile phone app (see Multimedia Appendix 1 for more information).

**Figure 8 figure8:**
[figure not shown]
Activity tracker connected to the mobile phone app (see Multimedia Appendix 1 for more information).

### Outcomes

Table 2 presents all outcome measures, the measurement instruments that will be used, and the time points when they will be assessed.

#### Primary Outcome

The primary outcome measure of the study will be time to return to normal activities (RNA). The Patient-Reported Outcomes Measurement Information System (PROMIS) Physical Functioning item bank version 1.2 will be used to measure limitations in daily activities. This item response theory (IRT)–based item bank has been developed and validated in the United States and translated into Dutch-Flemish [31,32]. Initial validation studies in Dutch patients confirmed the unidimensionality and underlying calibration of the IRT model (personal communication, article submitted). This item bank consists of 121 activities. We made a selection of the 29 most relevant activities for this study (Multimedia Appendix 2). We considered the 92 excluded activities as not being affected by the type of surgery (eg, “Can you brush your hair?”) or as duplicate activities. The list of 29 activities will be presented to the patients at baseline (prior to surgery), and they will be asked to select 8 activities which are most relevant for them in daily life. In this way, patients will design their own personal physical functioning short form. Since items in an IRT-based item bank are calibrated onto the same continuum, one can select any subset of questions in that bank and the scores obtained from the derived short forms are comparable to that from the complete bank [33]. In the follow-up questionnaires, patients will only receive those PROMIS questions regarding the 8 activities that they selected before surgery as relevant to their personal life. Items are scored on a 5-point scale with 1 as most limited and 5 as no limitation. In addition, they will be asked postoperatively whether they can perform this activity on the same level as before surgery. If they answer “yes,” they are asked to fill in since when (date), and the question will no longer be repeated in the following questionnaires. If the question is answered with a “no,” the question will be asked again at the next follow-up moment. For each patient, this will result in 8 dates of resumption of their activities. These dates will be converted into time periods by calculating the number of days that have elapsed between the date of surgery and the date of the resumption of that particular activity. The moment of resumption of the last activity on the list will be defined as the RNA moment and thus the primary outcome measure will be time elapsed between surgery and resumption of the last activity. If patients have not resumed 1 or more activities at 6 months, those activities will be censored. If information about the resumption of 2 or fewer activities is missing, the RNA moment will be calculated based on 6 activities. If information about the resumption of more than 2 activities is missing, the RNA moment cannot be calculated accurately and will be considered as missing data.

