### Allocation

After inclusion, patients will be asked to complete the first online questionnaire (T_0_) within the month before surgery. After patients have completed the questionnaire, randomization will take place by means of a computer-based randomization list stratified regarding hospital, sex, and surgical procedure using permuted blocks, size 2. Patients are randomized to the intervention or the control group in a 1:1 ratio. The researcher performing randomization is independent from the recruitment or data analyses.

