### Data Analyses

#### Effect Analyses

All analyses will be performed in SPSS (IBM Corp). Baseline characteristics will be summarized using descriptive statistics and compared between the intervention and control group using *t* tests, Mann-Whitney U tests, chi-square tests, or Fisher exact tests. Survival analysis will be used to analyze time until RNA data. Both crude and adjusted analyses will be performed. Hospital, surgical procedure, and sex will be taken into account as covariates in the adjusted analyses because these are the factors for which stratification will apply. In addition, when there are clinically relevant differences between the intervention and the control group in the baseline characteristics or potential confounding factors, this will also be considered as a covariate in further analyses. To describe the distribution of the duration until RNA in both groups, the Kaplan-Meier method will be used. The Cox proportional hazard model will be applied to calculate HRs. Differences in secondary outcomes between the groups will be assessed by mixed models and multilevel logistic regression models for outcomes that are measured more than once during follow-up, and *t* tests, Mann-Whitney U tests, chi-square tests, or Fisher exact tests will be used when differences on 1 time point will be compared. Statistical analyses will be performed according to intention-to-treat principle, which will be compared to per-protocol analyses. Patients will be included in the per-protocol analyses when they used the intervention as intended, which will be defined as the generation of a convalescence plan on the website. This will be measured by a web log. Subgroup analyses will be performed regarding the surgical procedure (1. Cholecystectomy, 2. Hernia inguinal surgery and 3. Adnexal surgery) and type of surgery (gynecological vs surgical procedures). A post hoc analysis will be carried out on patients without major complications (definition described in Potential Confounding Factors).

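### The adjusted Cox model lets in baseline prognostic variables only when the arms differ, so it gives up precision that the difficulty of the self-chosen activity list could supply

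*Protocol article*

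**What the plan says.** Under Primary Outcome, patients see 29 PROMIS physical functioning items at baseline, and "they will be asked to select 8 activities which are most relevant for them in daily life". After surgery they report, for each one, "whether they can perform this activity on the same level as before surgery", and since what date. The endpoint is then the latest of the eight dates: "The moment of resumption of the last activity on the list will be defined as the RNA moment".

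The same section supports the free choice of items by their common calibration, from which it concludes that "one can select any subset of questions in that bank and the scores obtained from the derived short forms are comparable".

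Under Allocation, the order of events is clear: "After patients have completed the questionnaire, randomization will take place". The list is therefore a pre-randomisation characteristic.

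Under Effect Analyses, crude and adjusted Cox analyses are both planned, and neither is named as the main one. The covariate rule has two parts. First, "Hospital, surgical procedure, and sex will be taken into account as covariates in the adjusted analyses", because randomisation is stratified on them. Second, further variables are considered "when there are clinically relevant differences between the intervention and the control group in the baseline characteristics or potential confounding factors". The Prognostic Factors section lists the T-score of the personal short form at baseline, but Effect Analyses does not make it a fixed covariate.

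**The concern.** An endpoint defined by the slowest of eight activities depends on which activities are on the list. The article itself expects activities to resume at different times: time to the first activity and time to 75% of them are separate secondary outcomes. Two patients who recover at the same rate can therefore have different endpoint times only because one listed something more strenuous.

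The trial will hold a measure of this for every patient before randomisation, and the covariate rule does not use it unless the arms happen to differ. That trigger looks at the wrong property. In a randomised trial, adjustment gains power because a covariate predicts the outcome. A strong predictor is worth including when it is perfectly balanced, and a weak one gains little even when it is unbalanced. The trigger also leaves the final model to be settled after the data are seen.

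What is at stake is precision on the primary outcome, in a design that is sized at 80% power with little to spare.

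**Working it through.** **The plan's own figures.** Inputs from Sample Size Calculation: HR 1.4, two-sided 5% log-rank test, 80% power, 285 events, 308 patients, 2.5% not returning, 5% dropout.

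- Freedman: (1.960 + 0.842)² × [(1.4 + 1)/(1.4 − 1)]² = 7.849 × 36 = 282.6, so 283 events.
- Schoenfeld: 4 × 7.849/(ln 1.4)² = 278 events.
- Power with 285 events: Φ(½ × √285 × ln 1.4 − 1.960) = Φ(0.88) = 81%.
- Total: 285/(0.975 × 0.95) = 307.7, so 308.

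The sample size reproduces.

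**Case A: 1.4 is the conditional HR.** The article does not say how strongly list difficulty predicts the endpoint, so its SD on the log-hazard scale is an assumption, shown over a range. Set-up: 293 evaluable patients (308 × 0.95), exponential times, 2.5% censored at the end, about 286 events, one normal covariate omitted or included, 3,000 simulated trials per row. With exponential times the covariate's share of the variance in log time is SD²/(SD² + π²/6).

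| SD | Share of log-time variance | HR, covariate omitted | Power, omitted | Power, true covariate included |
|---|---|---|---|---|
| 0 | 0% | 1.40 | 80% | 80% |
| 0.2 | 2% | 1.39 | 78% | 80% |
| 0.3 | 5% | 1.37 | 74% | 80% |
| 0.5 | 13% | 1.33 | 66% | 80% |
| 0.7 | 23% | 1.29 | 57% | 80% |
| 1.0 | 38% | 1.25 | 46% | 82% |

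Repeated simulations, which differ in random draws and in how dropout is handled, put power with the covariate omitted at 77-78% for SD 0.2, 73-78% for SD 0.3 and 65-69% for SD 0.5.

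**An imperfect covariate.** The last column assumes that the true prognostic value is measured without error. The calibrated location of an item is only a proxy for how long that activity takes to resume after surgery. At SD 0.5, power is 66% unadjusted, 69% with a proxy correlated 0.5 with the true value, 71% at 0.7, and 80% with the true value. The proxy thus recovers (69 − 66)/(80 − 66) = 21% to (71 − 66)/(80 − 66) = 36% of the loss.

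**A useless covariate.** When the covariate has no effect, including it leaves power at about 80%. A wrong guess costs practically nothing.

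**Case B: 1.4 is the marginal (unadjusted) HR.** Here the simulation works at item level: 8 of 29 items per patient, time to the last one, treatment effect set so that the unadjusted HR is about 1.4. Assumed SDs on the log-time scale are 0.7 for the patient's recovery rate, 0.4 for activity-level noise and 0.3 to 0.8 for the spread between items. The adjusted model uses the hardest and the mean item difficulty. There were 1,500 trials per row.

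| Log-time variance explained by list difficulty | Power, unadjusted | Power, adjusted |
|---|---|---|
| 3% | 80% | 83% |
| 8% | 80% | 83% |
| 18.5% (unadjusted HR came out at 1.42) | 85% | 90% |
| 57.5% | 81% | 98% |

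In this case nothing is lost against the plan. Adjustment adds power on top of it.

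**The case against.** The strongest reply is that nothing in the plan is invalid. The list precedes randomisation, so its difficulty is balanced on average. The crude HR is a valid marginal effect, and the type I error is unaffected. That stands.

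A reader might infer from Case A that the trial is underpowered or that its HR is biased towards 1. The documents do not support either. The move from 1.40 to 1.33 is non-collapsibility: the conditional and the marginal HR are different quantities. A shortfall against 80% follows only if 1.4 is conditional. Sample Size Calculation takes 1.4 from return to work in an earlier trial, pairs it with a log-rank test, and does not say which kind it is. The log-rank pairing leans, if anything, towards the marginal reading.

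A reader might also say that the model ignores baseline information. That is too strong. The three stratification factors are in the model, procedure and sex may carry part of the list's difficulty, and the imbalance rule could admit more.

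Nor does the article claim that times are comparable across lists. Its calibration statement speaks of scores, so that sentence needs no change. It simply gives no support for a time-to-last-activity endpoint.

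There are also reasons to expect a weak link. Resumption is judged against the patient's own earlier level, whereas calibration measures absolute difficulty. Items judged unaffected by the surgery were removed. If patients chose at random, 1 − C(22,8)/C(29,8) = 1 − 319,770/4,292,145 = 93% would hold at least one of the seven hardest items, which narrows the variation in the hardest one. Choice by preference could widen it again. These points bear on the size of the gain, not on its direction.

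Finally, covariates are often left to an analysis plan. Here, however, the article states the rule, and it is the stated trigger that is poorly chosen.

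**Conclusion.** The point holds as an inexpensive efficiency improvement. The covariate rule selects on observed imbalance when it should select on prognostic strength. It therefore leaves unused a pre-randomisation measure that plausibly predicts the primary endpoint. It is not a validity defect, and 285 events and 308 patients stand.

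The size cannot be determined from the article. It rests on two unknowns: the prognostic strength of list difficulty, and whether 1.4 is conditional or marginal. On the conditional reading the loss is about 2-3 points of power at SD 0.2 and 11-15 points at SD 0.5 (80% against 65-69%), of which a proxy would recover only part. On the marginal reading planned power is kept, and about 3 points are forgone when difficulty explains 3-8% of the variance in log time.

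**What to change.** In the adjusted Cox model, prespecify two baseline covariates next to hospital, procedure and sex, whatever the observed balance: the calibrated PROMIS location of the hardest activity selected at T0, and the baseline PROMIS T-score that is already listed as a prognostic factor. The two are not interchangeable, since the first describes the list and the second the patient's functioning. Keep the crude HR as planned.

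The data are already collected. The cost is one or two model parameters against about 285 events, and an adjusted HR that is conditional on these covariates and should be labelled so beside the crude one. The gain reaches the main conclusion only if the adjusted model is the one that carries it, so the plan should say which model does.
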